This article thus describes the design of a large evaluation study on the Happiness Route. Based on the pilot studies and practical experiences, we hypothesize that emotional, social and psychological well-being of participants of the Happiness Route will increase in comparison to the traditional and commonly-used problem-based approach and health care will decrease. Furthermore, we will study whether the intervention decreases loneliness, depressive symptoms and consumption of care and whether it increases purpose in life, resilience, social participation and health-related quality. Last, we will examine if characteristics of both participants and counselors have moderating effects. As we handle strict inclusion and exclusion criteria and all counselors will receive the same thorough training, we do not expect moderating effects.

Existing studies on positive psychological interventions mostly had a limited amount of participants, were carried out in experimental settings, and with rather privileged groups with no psychosocial problems, such as students
[16]. The present study will belong to the 10% of the largest trials on positive psychological interventions
[27]. It is among the first to examine such an intervention in a practice-based research setting with several partners in the field of social work. Our study is also among the first to use an outreaching approach to target individuals with an accumulation of risk factors for low levels of well-being: lower socioeconomic status, social isolation, and health limitations
[1-5]. The study will thus provide new insights into the opportunities for mental health promotion in realistic settings.

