#### Multivariate analyses

We will first do a missing data analysis for all participants on the second and third measurement point. A logistic regression analysis will be conducted with having complete data as the dependent variable, and demographic and psychosocial characteristics at baseline measurement as independent variables to assess non-random missings. We will use multiple imputations (five data sets) to replace missing values and carry out the analyses on the pooled data set. Hence, all participants who were randomized can be included in the statistical analyses. The results from this imputed intention-to-treat sample will be compared to the results of the observed data only.

We will use MANOVA analyses to assess the effectiveness of the intervention in reaching its primary and secondary outcomes. The measures at baseline, post-treatment, and follow-up are repeated measures and the experimental condition versus the control condition is the independent variable. In all analyses, we take into account that the observations are clustered as participants are ‘nested’ in each of the ten local institutions. Therefore, robust standard errors are computed using the first-order Taylor-series linearization method.

Standardized mean differences (Cohen's d) at post-intervention and follow-up are calculated as the difference between the means of the treatment and control condition divided by the standard error of the control condition. We expect a small to moderate effect size for the primary outcome (Cohen’s d= 0.35).

To answer the question on moderating participant factors, we will analyze the moderating effects of demographic characteristics (age, gender, and cultural background) on the effectiveness of the intervention. Following Kraemer et al.
[60], we will enter the change score of positive mental health at nine months minus baseline as a dependent variable in a linear regression model. The condition dummy (experimental versus control condition), the potential moderator, and their interaction are independent variables. When the interaction effect is significant, there is a differential effect of the intervention for this particular moderator. Analyses will be carried out for each of the three potential moderator variables separately.

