We do similar regression analyses to answer the question on moderating counselor factors. The potential moderators are the indices for work experience, work satisfaction, and adherence to the program as measured with the questionnaire for counselors and the logs of the counselors.

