### Power calculation and sample size

Based on a meta-analysis of previous studies in positive psychology, conducted with instruments that are similar to the MHC-SF
[27], we expect a small to medium effect size for the intervention Happiness Route (Cohen’s d = 0.35). A pilot study
[25] and experiences from previous practice showed that there are no negative effects on the well-being of participants. We therefore specified a one-tailed test with an alpha level of 0.05 under the assumption that the Happiness Route will be more effective than the Customized Care group, as the latter is not intended to improve positive mental health. This has also been shown in previous studies on positive psychological interventions
[27]. Given ethical considerations, Knottnerus and Bouter
[61] argued that one-sided testing is preferable under these circumstances. Power analysis with the program GPower with a power of 0.80 (1 – beta of 0.20), indicates that 102 participants are needed in each condition. We used a maximal drop-out rate of 20% which is a conservative estimate from previous experience. In everyday practice, the drop-out was about 10% of the more than 500 people who already participated in a Happiness Route. With a maximal drop-out of 20%, we need 128 participants in each condition, 256 in total.

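### Each of six separately tested interactions is read as a real differential effect if significant, which leaves a sizeable chance of a false moderator claim when benefit is uniform (secondary analyses only)

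*Protocol article*

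**What the plan says.** The moderator analysis is set out in the protocol article under Multivariate analyses. For participants, "we will analyze the moderating effects of demographic characteristics (age, gender, and cultural background) on the effectiveness of the intervention". The dependent variable is the change in positive mental health from baseline to nine months. The model contains condition, the moderator and their product. The reading of the result is fixed in one sentence: "When the interaction effect is significant, there is a differential effect of the intervention for this particular moderator". The next sentence adds: "Analyses will be carried out for each of the three potential moderator variables separately".

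The counselor side follows by reference: "We do similar regression analyses to answer the question on moderating counselor factors", and "The potential moderators are the indices for work experience, work satisfaction, and adherence to the program". That makes six interaction tests in all.

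The authors do not expect any of them to be positive. The Background says that "all counselors will receive the same thorough training, we do not expect moderating effects". The Discussion repeats the expectation for participants and for counselors, and says that the moderator analyses are there to test it.

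The only significance level in the article is under Power calculation and sample size: "We therefore specified a one-tailed test with an alpha level of 0.05". It belongs to the main comparison. No level and no sidedness is given for the interaction tests.

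**The concern.** The rule turns a p-value directly into a statement of fact, one moderator at a time, with no allowance for there being six chances. The question the authors pose is a joint one: is benefit uniform across participants and counselors? A single significant interaction is enough to contradict that. The relevant error is therefore the chance that at least one test is significant when none should be, and this exceeds the per-test level.

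At stake is a secondary conclusion of the trial. A chance interaction, for example with cultural background or counselor experience, would be reported as showing that the intervention works differently in different people or hands. It would wrongly overturn the authors' own hypothesis of uniform benefit.

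**Working it through.** **Step 1. What the stated 0.05 refers to.** Inputs from Power calculation and sample size: d = 0.35, one-tailed alpha 0.05, power 0.80, drop-out 20%.

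- Normal approximation: n = 2 × (1.645 + 0.842)² / 0.35² = 100.9, so 101 per arm.
- Exact one-sided t-test: 102 per arm, power 0.801. This matches the article.
- With drop-out: 102 / 0.80 = 127.5, so 128 per arm and 256 in total. This also matches.
- A two-sided t-test would need 130 per arm, which does not match.

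The 0.05 is therefore the one-sided level of the main comparison. Carrying it over to the interactions is an assumption.

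**Step 2. Chance of at least one false declaration, independent tests.** With k tests at level a and no true moderation, the chance is 1 − (1 − a)^k. It depends only on the per-test level, not on sidedness.

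| Tests | Level per test | Chance of at least one |
|---|---|---|
| 3 (one set) | 0.05 | 1 − 0.95³ = 14.3% |
| 6 (both sets) | 0.05 | 1 − 0.95⁶ = 26.5% |
| 6 (both sets) | 0.025 | 1 − 0.975⁶ = 14.1% |
| 6, Bonferroni | 0.05/6 = 0.0083 | 1 − (1 − 0.0083)⁶ = 4.9% |

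**Step 3. Correlated tests.** Simulated two-sided 0.05 tests with equal correlation r between all six statistics:

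| r | Chance of at least one |
|---|---|
| 0 | 26.5% |
| 0.3 | 24.2% |
| 0.5 | 20.7% |
| 0.7 | 16.4% |

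If only the three counselor statistics are correlated, the chance is 25.9% (r = 0.3), 25.1% (r = 0.5) or 23.6% (r = 0.7).

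**Step 4. The regressions themselves.** The planned model (condition, moderator, product) was simulated with a uniform effect of 0.35, total N of 204 or 256, and moderators correlated 0 to 0.5 within the participant set and within the counselor set. Counselor values were shared by that counselor's participants. At least one of the six interactions was significant in 24.4% to 27.1% of runs. For the participant set alone it was 13.2% to 14.5%. Cultural background was treated as a single yes/no term, which is an assumption. Ordinary standard errors were used, not the robust ones that the article plans for clustering by institution.

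**Step 5. Power of one interaction test.** Assumptions: moderator split evenly, change-score SD of 1, true interaction 0.35 (as large as the whole expected effect), 204 analysed, so 51 per cell.

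- Standard error = √(4/51) = 0.28, and 0.35 / 0.28 = 1.25.
- Two-sided power at 0.05: P(Z > 1.96 − 1.25), about 24%.
- Two-sided power at 0.0083: P(Z > 2.64 − 1.25), about 8%.

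**The case against.** Several objections carry weight.

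- **No level is stated.** A reader might infer that the plan tests six moderators at the full 0.05 and so exceeds its own stated error rate four- or fivefold. The documents do not support that. The 0.05 is given for the sample size only, and every percentage above depends on the level assumed. This stands.
- **The family of six is a choice.** The article poses two questions, one about participants and one about counselors, and draws its inference per moderator. Taken per question, the figure is about 14%. This stands, so both figures are given.
- **It may be left to the analysis plan.** A condensed article need not spell out multiplicity handling, and the sentence could be read as merely explaining what an interaction coefficient means. This stands only in part. Silence on adjustment would be no finding. But the sentence is worded as a decision rule, and an analysis plan that added an adjustment would be changing it.
- **The set is short and prespecified.** The article narrows a long list of characteristics to six. For participants it also fixes the outcome and time point. That limits selective reporting but does not change the arithmetic.
- **Strict adjustment can defeat the purpose.** The tests exist to challenge the authors' preferred assumption. Cutting power from about 24% to about 8% makes that assumption harder to refute. This stands against making Holm compulsory.
- **Consequences.** A reader might infer that municipalities would restrict who takes part or who counsels. Nothing in the article says so; the Discussion ties uptake to overall superiority and lower care use.

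**Conclusion.** The point holds as a minor one. The decision sentence, applied to six separate tests, would often yield a false claim of moderation if the authors' expectation of uniform benefit is correct. The chance is about 14% within each set of three and about 21% to 27% across all six, assuming 0.05 per test. It is about 14% across six if 0.025 is used. The lower end of the 0.05 range needs a correlation of about 0.5 between all six statistics, including between participant and counselor traits; weaker correlation puts the figure nearer 24% to 27%.

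Low power adds to the problem: under the assumptions shown, a single significant interaction is weak evidence, yet the rule treats it as settled.

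This reaches only the secondary moderator conclusions. The well-being comparison between the Happiness Route and Customized Care is untouched. Higher rates, about 34% to 41%, arise if outcomes also cluster by counselor and this is ignored. They rest on assumed intraclass correlations of 0.05 to 0.10 and 20 counselors per arm, which the article does not give, so they form no part of the conclusion.

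**What to change.** Under Multivariate analyses, replace the sentence that equates a significant interaction with a differential effect, and make the replacement cover the counselor analyses too. Suggested text: *The six interaction analyses (three participant and three counselor moderators) are exploratory. Each interaction will be reported as an estimate with a 95% confidence interval, and no differential effect will be declared from an unadjusted p-value.*

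If the sponsor wants a formal declaration, state the significance level and sidedness and apply Holm's procedure across the six tests (first step 0.05/6 = 0.0083). The price is the loss of power shown above.

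The exploratory wording costs two sentences, with no new data and no change to the sample size. What is given up is the ability to present a moderator as established by this trial alone.

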### Setting

The study will be carried out in the field of healthcare and social work in nine municipalities in the Netherlands by the University of Twente and Arcon, an organization in the welfare sector. The study is funded by ZonMw (the Netherlands Organisation for Health Research and Development) under the prevention program. A municipal officer will generally be the local project leader, but in some cases, the local project leader works in one of the participating institutions. The local project leader is responsible for the recruitment through intermediaries, the allocation of participants to counselors and for the final approval on spending the budget in the Happiness Route. Municipalities mostly provide financial support for the training of counselors, the appointment of the local project leader, as well as the budget for the Happiness Routes. In other cases, the project is financed by social funds.

The recruitment of participants will be carried out by intermediaries who work as professionals in local care and social work institutions. Examples of intermediary organizations and professions are home care, housing associations, after-care nurses, psychiatric nurses, religious institutions, well-being institutions and organizations for people with mental disabilities. Intermediaries are in direct contact with the target group in their daily work. They can suggest possible candidates to the local project leader, who informed the intermediaries about the study and the target group.

Counselors are experienced professionals, such as social workers, and in some cases experienced volunteers. They are responsible for the intake and the delivery of the experimental and control interventions. To avoid contamination between the experimental and the control conditions, counselors will only deliver interventions in one of these conditions. Both counselors providing the Happiness Route and counselors providing the control condition will receive suitable training.

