### Randomization

When the written informed consent and the baseline questionnaire are received by regular mail, inclusion will be carried out on the basis of the criteria. Each included participant will be appointed randomly to either the intervention or the control condition, based on an a priori computer-generated randomized number list. No stratification will be carried out.

The principal investigator informs the local project leader of the outcomes of the inclusion and randomization procedure, so that the local project leader can appoint a counselor to deliver the intervention in the experimental condition (Happiness Route) or the control condition (Customized Care). It is not possible to blind the conditions to the counselors.

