#### Moderating measures

To address the question whether the effect of the intervention is different for participants with varying backgrounds, we will examine whether age, gender, and cultural background moderate the effectiveness of the intervention. To address the question whether the effect of the intervention depends on the characteristics of counselors, we will examine the moderating effects of the characteristics of counselors: work experience, work satisfaction, and adherence. For *work experience* we will compute an index that is based on educational level and number of years’ experience. For *work satisfaction*, we will compute an index that is based on work engagement
[49] and job satisfaction
[50,51]. Furthermore, counselors will fill out online logs for each participant after every home visit. These logs can be used to measure *adherence*.

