This is the first study to describe the evaluation of a practice-based program that nudges a target group suffering from health problems and low SES out of their social isolation towards more well-being by a happiness-based approach. Our study will answer questions concerning the effectiveness of this happiness-based approach. We will follow an intervention in practice, from recruitment, intake, and inclusion up to conducting the intervention and measuring effects. We will not only take a closer look at the effects of the Happiness Route, but also study if participants benefit in a similar way. We expect that the inclusion criteria will make sure that the intervention is beneficial to all included participants. We also assume that counselor characteristics will not influence the effectiveness of the intervention, as we train them all in a similar way. To test these assumptions, we will examine the role of characteristics of both participants and counselors. Another strength of this study is the expected high external validity, as the intervention will be examined in a real-life setting and the recruitment for the study is the same as the actual recruitment for the Happiness Route.

However, this RCT also has some limitations. Firstly, the available time to detect a possible change in the outcome measures will be only nine months in total (from intake to follow-up measure) and only six months after the intervention ended. Some changes, especially in the consumption in health care, might only take place later in time, also because institutions are often slow in changing care schemes, such as domestic help. Nine months are however a standard time for follow-up in psychological research. In fact, many studies in the field of positive psychology do not satisfy this standard and use no or shorter follow-up measurements
[16].

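### For counselor work experience and satisfaction, the interaction alone cannot show whether Happiness Route results depend on who delivers it; both arm-specific slopes should be reported beside it.

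*Protocol article*

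**What the plan says.** Under Moderating measures, the article sets the aim: "To address the question whether the effect of the intervention depends on the characteristics of counselors". The Discussion states the expectation to be tested: "We also assume that counselor characteristics will not influence the effectiveness of the intervention, as we train them all in a similar way".

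Under Multivariate analyses, one moderator model is written out, for participant traits. The outcome is the nine-month minus baseline change in positive mental health. "The condition dummy (experimental versus control condition), the potential moderator, and their interaction are independent variables". The reading is: "When the interaction effect is significant, there is a differential effect of the intervention for this particular moderator". The counselor analysis follows in one sentence, "We do similar regression analyses to answer the question on moderating counselor factors", and then names the indices for work experience, work satisfaction and adherence. No other model or reading is given for counselors.

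Two design features matter here. Under Setting, to avoid contamination, "counselors will only deliver interventions in one of these conditions". Under Randomization, the local project leader appoints the counselor once the allocation is known. Only the allocation to condition is random; the pairing of participant and counselor is not.

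**The concern.** Age, gender and cultural background exist before allocation, are balanced by randomization in expectation, and have one value for a participant whichever arm is drawn. For these, the interaction has its usual meaning.

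A counselor trait has none of these properties. It belongs to the person appointed after allocation. The two arms draw on disjoint groups of counselors, who do different work. The regression can still be fitted, but its interaction compares two groups of people with no counselor in common.

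The Discussion says the analysis will test whether counselor characteristics leave effectiveness untouched. If only the interaction is read, a null result could be taken to mean that the choice of Happiness Route counselor does not matter, and a significant result to mean that it does. Neither follows. The question has practical weight, because counselors range from social workers to experienced volunteers.

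The point covers work experience and work satisfaction, and it arises even if both are measured perfectly and identically in the two arms. Adherence raises separate measurement questions and is left aside.

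**Working it through.** **Inputs from the article.** 102 participants per condition, 128 after allowing for drop-out; the three-term regression; counselors nested in one condition; appointment after allocation.

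**The article's own figure.** It gives none for this analysis. The sample size reproduces: a one-sided t-test at 0.05 with d = 0.35 needs 102 per arm (power 0.801); 102 / 0.80 = 127.5, so 128 per arm and 256 in total. It is not in dispute.

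**Algebra.** Let G = 1 for the Happiness Route and 0 for Customized Care, and let X be the counselor index in SD units:

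E[Y] = a + t·G + bC·X + (bH − bC)·G·X

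- Slope in Customized Care (G = 0): bC.
- Slope in the Happiness Route (G = 1): bC + (bH − bC) = bH.
- Interaction: bH − bC.

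So the interaction is zero whenever bH = bC, however large both are, and it is nonzero when bH = 0 and only bC differs from zero. This needs no assumed figures.

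**Illustration.** Assumptions not in the article: residual SD 1, two-sided 0.05, no counselor variance beyond the trait, slope 0.25 SD per SD of X. With n per arm:

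- SE(interaction) = √(2/n): √(2/128) = 0.125; √(2/102) = 0.140.
- SE(Happiness Route slope) = √(1/n): √(1/128) = 0.0884; √(1/102) = 0.0990.

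At n = 128, a true interaction of 0.25 in size gives z = 0.25/0.125 = 2.00 (52% significant). A true within-arm slope of 0.25 gives z = 0.25/0.0884 = 2.83 (81%). At n = 102 the z values are 1.79 (43%) and 2.52 (71%).

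| True slopes (bH, bC), n = 128 | Interaction significant | Happiness Route slope significant |
|---|---|---|
| 0.25, 0.25 | 5% | 81% |
| 0, 0.25 | 52% | 5% |
| 0.25, 0 | 52% | 81% |

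The second and third rows have the same interaction column, although counselors matter in a different arm in each. Only the within-arm slopes tell them apart.

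**Simulation check.** With an assumed 20 counselors per arm (1,500 replicates), the first row came out at 5.0% and 79.1%, and the second at 50.9% and 4.4%. At 102 per arm these were 5.8% and 69.4%, and 42.3% and 4.5%. With slope 0.3, the closed form gives 5% and 92% for equal slopes and 67% for the interaction with a control-only slope (n = 128). With slope 0.3, 102 per arm and 10, 25 or 50 counselors per arm, simulation gave 4–5% and 74–84% for equal slopes, and 48–55% and about 5% for a control-only slope.

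**Counselor clustering.** With an assumed counselor intraclass correlation of 0.05 and 10 counselors per arm, errors that ignore counselors make both the interaction and the Happiness Route slope significant about 10% of the time when both slopes are zero.

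**The case against.** The strongest reply is that an intervention effect is a contrast. The Background and Discussion define success in comparison with the problem-based approach, and the wording under Moderating measures can be read the same way. Moderation of a contrast is a difference in slopes, which is what the interaction tests.

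This stands, and it blocks a stronger reading. A reader might infer from the table that the planned rule misses moderation when slopes are equal, or declares it falsely about half the time when only control counselors matter. The article does not support that. Take the simulated condition effect, t = 0.35. With equal slopes the contrast is 0.35 at every X, so finding no moderation of the contrast is correct. With bH = 0 and bC = 0.25 the contrast is 0.35 − 0.25X: 0.60 at X = −1 and 0.10 at X = +1. It really does vary, and 51% is power, not a false-positive rate.

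A second fair reply is that a within-arm slope is no cleaner. If project leaders send participants with a better outlook to experienced counselors in both arms, that shared selection cancels in the interaction but enters each within-arm slope in full. The slopes therefore cannot replace the interaction.

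A third reply is that arm-specific slopes are a reporting detail that an article may leave to a fuller plan. This weighs less, because the article does fix a reading for its only moderator model and passes that model to counselors unchanged.

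What remains is that the contrast read from the interaction refers to changing the trait in both arms together. If only the Happiness Route is staffed differently, the contrast shifts by bH, and the interaction alone does not give bH.

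**Conclusion.** The point holds in limited form. For counselor work experience and work satisfaction, the interaction validly compares two slopes, but by itself it does not settle the Discussion's assumption that counselor characteristics do not influence effectiveness. A null interaction is compatible with large equal slopes. A significant one can arise entirely from Customized Care counselors. Nor is it a randomized differential effect, because counselors are neither shared between arms nor randomly paired with participants.

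The algebra rests only on the stated model and the nesting. The percentages rest on assumed slopes, counselor numbers and clustering, and illustrate only what the interaction responds to. The conclusion also takes the counselor model to be the participant model, the only one the article writes out. This is a secondary analysis; the primary comparison and the sample size are unaffected.

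**What to change.** Keep the planned interaction. For work experience and work satisfaction, add a sentence committing to the following, all from the same regression:

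- Report the slope within the Happiness Route (moderator main effect plus interaction, with Customized Care as reference) and the slope within Customized Care, each with a confidence interval that allows for clustering by counselor.
- For counselor traits, describe the interaction as the difference between the two slopes, not as a differential effect of the intervention.
- Draw conclusions about counselor influence from all three quantities together, and label all three as observational.

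On clustering, the article applies robust errors for the ten local institutions in all analyses. These may already absorb counselor clustering if each counselor stays within one institution, which the article does not say. With few counselors a small-sample method is advisable: counselor-clustered errors with 20 counselors per arm were somewhat liberal in simulation (7–10% under the null), whereas a regression on counselor means stayed at about 4–6%.

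The cost is a sentence or two, with no new data or model. The downside is that the within-arm slopes are open to confounding by how project leaders assign counselors, including selection common to both arms that would cancel in the interaction. They should supplement the interaction, not replace it.
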